**Figure 5 F5:**
[figure not shown]
Diagram of Bazheng acupoints.

**Figure 6 F6:**
[figure not shown]
Diagram of Heche road.

**Table 2 T2:** Location of acupoints for pestle needle therapy.

Acupoint	Location
Eight array acupoints of Shendao (DU11)	Using Shendao (DU11) as Zhong Gong (DU11 is located in the depression below the spinous process of the 5th thoracic vertebra), the distance from Shendao (DU11) to Shentang (BL44) is the radius.
Eight array acupoints of Yaoyangguan (DU3)	Using Yaoyangguan (DU3) as Zhong Gong (DU3 is located in the depression below the spinous process of the 4th lumbar vertebra), the distance from Yaoyangguan (DU3) to Dachangshu (BL25) is the radius.
Heche Road of Da zhui (DU14) to Changqiang (DU1)	The posterior median line from Da zhui (DU14) to Changqiang (DU1) and 3 parallel lines on each side of the posterior median line, 7 lines in total.
Zhangmen (LR13)	In the mid-axillary line, below the end of the 11th rib.
Sanyinjiao (SP6)	On the inner side of calf, 3 cun above the tip of inner ankle, at the posterior border of the medial edge of tibia.
Taichong (LR3)	Dorsal side of foot, posterior depression of the 1st metatarsal space.
Tianshu (ST25)	Two cun next to the anterior median line, level with the middle of navel.
Zusanli (ST36)	On the outer side of the lower leg, 3 cun below Dubi (ST35).
Shangjuxu (ST37)	On the outer side of the lower leg, 6 cun below Dubi (ST35).
Xuehai (SP10)	Bend the knee, on the inner thigh, 2 cun above the medial end of patellar base, at the bulge of the medial head of quadriceps.
Weizhong (BL40)	Midpoint of the transverse popliteal line.
Chengshan (BL57)	In the middle of the back of calf, between Weizhong (BL40) and Kunlun (BL60), in the depression under the belly of the gastrocnemius muscle when the calf is straightened and the heel is lifted.
Baliao acupoint	①Shangliao (BL31): In the sacral region, between the posterior superior iliac spine and the posterior median line, at the first posterior sacral foramen. ②Ciliao (BL32): In the sacral region, below the internal posterior superior iliac spine, at the second posterior sacral foramen. ③Zhongliao (BL33): In the sacral region, medial to Ciliao (BL32), at the third posterior sacral foramen. ④Xialiao (BL34): In the sacral region, below the inner part of Zhongliao (BL33), at the fourth posterior sacral foramen.

###### Tuina treatment

2.5.1.2.2

Treatment techniques include Zhian, Moyun, Zhirou, and Tinie (Table 3). The criteria for the selection of acupoints refer to the book “Tuina Studies” published by the Chinese Press of Traditional Chinese Medicine.^[49]^ The number of acupoints selected for this therapy is 12 (Table 4). The operation steps are as follows: ① The patient is placed in a supine position and Zhirou technique is applied to Zhongwan (RN12), Guanyuan (RN4), Qihai (RN6), Tianshu (ST25), Daheng (SP15) in turn. ② Place the patient in a prone position, apply Tinie technique to Changqiang (DU1) and Zhirou technique to Pishu (BL20), Weishu (BL21), Ganshu (BL18), Dachangshu (BL25). ③ Apply Zhian technique to Shenshu (BL23), Changqiang (DU1), and Moyun technique to Baliao acupoint. The frequency of treatment is about 20 minutes once a day, 5 days a week and the duration is 4 weeks.

**Table 3 T3:** The detailed methods of treatment techniques for Tuina.

Treatment techniques	Detailed methods
Zhian	Use the end of thumb to apply vertical pressure to the body surface. When a single finger is not strong enough, the thumb of the other hand can be overlapped to complement the pressure. It is often used in combination with Zhirou.
Moyun	Gentle rubbing movements with fingers, palm roots, thenar, or hypothenar muscles on the surface of body, either in a centrifugal or centripetal direction.
Zhirou	Apply the abdomen of fingers (thumb, middle finger, index finger, middle finger, or ring finger) to a certain area or acupoint and rub it in a gentle, rhythmic motion.
Tinie	Use thumb and other 4 fingers to make a squeezing motion on the surface of body.

**Table 4 T4:** Location of acupoints for Tuina.

Acupoint	Location
Zhongwan (RN12)	On the anterior median line of body, 4 cun above the navel.
Guanyuan (RN4)	On the anterior median line of body, 3 cun below the navel.
Qihai (RN6)	On the anterior median line of body, 1.5 cun below the navel.
Tianshu (ST25)	Refer to Table 2.
Daheng (SP15)	Four cun next to the anterior median line of body, level with the middle of the navel.
Pishu (BL20)	In the back, 1.5 cun next to inferior end of the spinous process of the 11th thoracic vertebra.
Weishu (BL21)	In the back, 1.5 cun next to inferior end of the spinous process of the 12th thoracic vertebra.
Ganshu (BL18)	In the back, 1.5 cun next to inferior end of the spinous process of the 9th thoracic vertebra.
Dachangshu (BL25)	In the back, 1.5 cun next to inferior end of the spinous process of the 4th lumbar vertebra.
Shenshu (BL23)	In the back, 1.5 cun next to inferior end of the spinous process of the 2th lumbar vertebra.
Changqiang (DU1)	In the depression below the tip of tailbone.
Baliao acupoint	Refer to Table 2.

###### Functional exercise

2.5.1.2.3

① Explain the importance of functional exercise and instruct the patient to perform abdominal breathing for 40 times. ② Instruct the patient to massage abdomen clockwise with the base of palm until skin is slightly red. ③ Instruct the patient to perform straight leg raising for 15 to 20 times, bridge-style movement for 5 to 10 times and hip contracting exercise for 10 to 15 times, then relaxing after lasting 5 seconds each time. ④ Pull the anal sphincter horizontally and vertically for 10 to 15 times respectively. ⑤ Finger stimulation for 15 to 20 seconds until the bowel wall is relaxed and feces flows. ⑥ Instruct the patient to simulate defecation. The frequency of treatment was once a day, 5 days a week and the duration is 4 weeks.

#### Criteria for discontinuing or modifying allocated interventions

2.5.2

If the patient suddenly develops other serious illnesses or requests to withdraw from the trial voluntarily, the interventions will be discontinued.

#### Strategies to improve adherence to interventions

2.5.3

All treatment and care measures will be carried out by clinically experienced doctors, therapists, and nurses. Before the trial begins, they will receive training to ensure that all interventions are completed with high qualities.

### Outcomes

2.6

#### Plans for assessment and collection of outcomes

2.6.1

Demographic and baseline data will be measured by questionnaires before the interventions. The primary outcome and secondary outcomes will be measured by checklists or scales. They will be assessed before the interventions, after 2 weeks of interventions and after 4 weeks of interventions.

#### Primary outcome

2.6.2

The primary outcome is the number of spontaneous bowel movement per week. It is defined as the number of spontaneous and complete bowel movement without the need of medication or manipulation. The trial investigator will use diary cards to count the number of spontaneous bowel movement in a week.

#### Secondary outcomes

2.6.3

(1)Stool characteristics: it will be evaluated with Bristol stool form scale,^[50]^ which is scored by typology. One point means type 1, 2 points means type 2, and so on. Type 1 is separate hard lumps, like nuts (hard to pass); type 2 is sausage-shaped but lumpy; type 3 is like a sausage, but with cracks on surface; type 4 is like a sausage or snake, smooth, and soft; type 5 is soft blobs with clear-cut edges (passed easily); type 6 is fluffy pieces with ragged edges, a mushy stool; and type 7 is watery, no solid pieces.(2)Degree of difficulty in defecation: it will be evaluated with scoring method by checklists. One point means no difficulty; 2 points means that force is required to pass the stool; 3 points means very strong force is required to pass the stool; 4 points means the aid of massage around the belly or even hand picking are required to pass the stool.^[51]^(3)Level of anxiety: it will be evaluated with anxiety self-rating scale.^[52]^ The scale include 20 items and adopts 4-grade scoring method, 1 point means no or very little time, 2 points means little time, 3 points means a lot of time and 4 points means most or all of the time. Calculation method: crude score is calculated first, then crude score is multiplied by 1.25 to obtain standard score, which is >50 as having anxiety symptoms, the higher the score, the more severe the symptoms.(4)Level of depression: it will be evaluated with self-rating depression scale.^[53]^ It has the same number of items, scoring method, and calculation method as self-rating scale.(5)Level of self-efficacy: it will be evaluated with general self-efficacy scale.^[54]^ The scale include 10 items and adopt 4-grade scoring method, 1 point means not at all correct, 2 points means somewhat correct, 3 points means mostly correct, 4 points means completely correct. Calculation method: total score is 10 to 40, with 0 to 19 being low, 20 to 29 being medium, and 30 to 40 being high. Higher scores indicate a stronger sense of self-efficacy.

### Data management and confidentiality

2.7

All patients will be numbered according to the order of admission time and randomly grouped. To avoid the occurrence of measurement bias, relevant data were collected by uniformly trained individuals who were not involved in the intervention process and were not aware of the groups. All data obtained from NBD patients will be recorded on case record form and entered into the software SPSS25.0. Two different individuals will enter data to ensure the accuracy. The obtained data, including checklists, scales, questionnaires, and informed consent forms will be stored in locked file cabinets, and will be kept strictly confidential. Only researchers will have access to the participants’ data in the study.

### Sample size

2.8

In this study, the following formula was selected to estimate the sample size:$$n=\frac{2{\left(\mu_{\alpha }+\mu_{\beta }\right)}^{2}P(1-P)}{\delta^{2}},P=(P_{1}+P_{2})/2$$

*P*_1_ is the effective rate of intervention group, *P*_2_ is the effective rate of control group. Based on pre-experimental results, *P*_1_ = 85%, *P*_2_ = 50%. According to statistical requirements, the *α* was set to 5%, and the *β* was set to 80%. By looking up the table of random numbers, we get $\mu_{\alpha }$ at 1.96, $\mu_{\beta }$ at 0.84, the estimated sample size was 28 patients per arm. To ensure the replenishment of lost samples, the sample content is increased by 20%, so the final sample size was 30 patients per arm.

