### Randomization and blinding

2.4

Randomization will be based on a randomization sequence generated by the software SPSS25.0. Patients will be randomized at a 1:1 ratio into intervention group and control group. Randomization will be performed by a statistician who is not involved in this study. Data managers, and outcome assessors will be unaware of the outcome. However, due to the trail's nature, the doctors, nurses, and therapists will not be blinded.

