### Statistical analysis

2.9

The software SPSS25.0 was used for statistical analysis of data. The statistician will be blinded to the whole trial process. The continuous variables will be showed as the mean ± standard deviation and performed with a paired samples *t*-test or independent *t*-test. The categorical variables will be presented as percentage (%), and performed with Pearson Chi-squared test. For all comparisons, if a *P*-value is less than .05, the difference is considered statistically significant.

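### The sample size is calculated for an effective rate that is not among the trial's outcomes, so the power of the primary comparison (weekly spontaneous bowel movements) is unknown

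*Protocol article*

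**What the plan says.** Section 2.8 (Sample size) uses a formula for two proportions. P1 "is the effective rate of intervention group" and P2 is its counterpart in the control group. The values are 85% and 50%, introduced with "Based on pre-experimental results". Alpha "was set to 5%, and the" beta is printed as 80%, with quantiles 1.96 and 0.84. The result is that "the estimated sample size was 28 patients per arm", and then "the sample content is increased by 20%, so the final sample size was 30 patients per arm".

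Section 2.6.2 reads: "The primary outcome is the number of spontaneous bowel movement per week". It defines this outcome as a number taken from diary cards and gives no cut-off that makes a patient a responder. The abstract names the same primary outcome. The secondary outcomes in section 2.6.3 are stool form, difficulty of defecation, anxiety, depression and self-efficacy, each a scale or score.

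Section 2.9 sets tests by type of variable: "The continuous variables will be showed as the mean ± standard deviation and performed with a paired samples" *t*-test or an independent one, and categorical variables go to Pearson chi-squared. It does not name a test for the primary outcome.

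**The concern.** A sample size calculation supports a power statement only for the endpoint and test it was made for. Here the endpoint that was sized appears in section 2.8 and nowhere else in the article, while the endpoint on which the trial will be judged does not enter the calculation. No expected difference in weekly bowel movements is given, and no SD.

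What is at stake is how the primary result will be read. If the groups do not differ significantly on the weekly count, nothing in the article tells a reader which differences the trial could have detected. The 85% vs 50% assumption cannot fill that gap, because the article does not say how an effective case relates to the count.

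**Working it through.** **1. Reproduce the article's figure.** Inputs from section 2.8: P1 = 0.85, P2 = 0.50, so δ = 0.35 and P = (0.85 + 0.50)/2 = 0.675; quantiles 1.96 and 0.84.

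n = 2(1.96 + 0.84)² × P(1 − P)/δ² = 2 × 7.84 × 0.675 × 0.325 / 0.1225 = 3.4398 / 0.1225 = 28.08.

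This matches the reported 28 (29 if rounded up). The 1.96 shows a two-sided 5% level. The 0.84 shows that 80% power was used, although the text prints that figure as beta.

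**2. What this calculation supports.** It supports a comparison of two proportions. For 85% vs 50%, the power of that comparison is about 82% at 28 per arm, 84% at 30 and 75% at 24.

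**3. Look for the same endpoint among the outcomes.**

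| Section | Quantity | Type |
|---|---|---|
| 2.8 | Effective rate | Proportion, not defined |
| 2.6.2 | Weekly spontaneous bowel movements (primary) | Count, no cut-off |
| 2.6.3 | Five secondary outcomes | Scales or scores |

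No rule in sections 2.6 or 2.9 turns the count into a proportion.

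**4. What the planned numbers give for the primary outcome.** Allocation is equal ("Patients will be randomized at a 1:1 ratio into intervention group and control group"), with 30 per arm. Assumptions: an independent two-sample t-test (the natural reading of section 2.9 for a comparison between groups), two-sided 5%, week 4 as the time point, and a standardised difference d = mean difference/SD, which the article does not give. Power comes from the noncentral t distribution with 2n − 2 degrees of freedom and noncentrality d√(n/2). The case of 24 per arm takes the section's 20% as loss from 30: 30 × 0.8 = 24.

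Difference detectable with 80% power:
- Normal approximation, 2.8 × √(2/n): 0.72 SD at n = 30 and 0.81 SD at n = 24.
- Noncentral t: 0.736 SD at n = 30 and 0.826 SD at n = 24.

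Power over a range of assumed d:

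| d | 30 per arm | 24 per arm |
|---|---|---|
| 0.3 | 21% | 17% |
| 0.5 | 48% | 40% |
| 0.6 | 63% | 53% |
| 0.8 | 86% | 77% |
| 1.0 | 97% | 92% |

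The article gives no basis for choosing a row.

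**The case against.** **The full protocol may define the effective rate.** It may, and the missing definition alone would be a weak point in a condensed article. The mismatch does not depend on it. The article states its sample size basis and its outcomes, and a definition kept elsewhere would not make the effective rate the primary outcome.

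**The t-test is not named for the primary outcome.** Correct: it is inferred from the rule for continuous variables, and chi-squared is available for categorical ones. The detectable differences above depend on that inference. The mismatch does not, since a count analysed by any method for means or counts is not a proportion.

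**The trial may be well powered.** This stands. A reader might infer from the mismatch that the trial is underpowered, but nothing in the article shows it: power equals 80% at d = 0.74 and exceeds it above that. The opposite inference fails as well. If effective were a cut on a normally distributed outcome, 85% vs 50% would correspond to 1.04 SD and power of about 98% at 30 per arm (94% at 24). The article does not say that effective is a cut on the count, and normality is doubtful for a low weekly count, so no conclusion should rest on that figure.

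**An undefined rate could become the headline result.** A reader might suspect this. The article does not support it: the abstract and section 2.6.2 name the same primary outcome, registration (December 2020) precedes the planned start (March 2021), and no effective rate is announced as a result. Defining the rate in advance is a precaution.

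**Conclusion.** The point holds as a mismatch between the endpoint that was sized and the primary endpoint. The arithmetic behind 28 per arm is sound, but it belongs to a comparison of proportions that is not among the listed outcomes. The implied 80% power therefore lacks support for the primary comparison; it has not been shown to be false. On the assumptions in step 4, the planned 60 patients give 80% power for differences of about 0.74 SD, or about 0.83 SD with 24 per arm remaining. Whether a true effect of that size is plausible cannot be judged from the article. The printing of beta as 80% and the step from 28 to 30 under a 20% allowance are separate matters and play no part in this conclusion.

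**What to change.** 1. Restate section 2.8 for the weekly count at week 4. Give the difference detectable with 80% power by a two-sided 5% t-test for the fixed 60 patients: about 0.74 SD with 30 per arm, and about 0.83 SD if 20% are lost and 24 per arm remain.
2. If the pre-experimental data contain a mean difference and SD for the count, report them with the power they imply at this sample size. If that power is below 80%, say so.
3. If an effective rate will be reported, define its threshold before any data are seen and list it in section 2.6.3 as a secondary outcome. Otherwise, do not present 85% vs 50% as the power basis for the primary outcome.

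Making a defined responder rate the primary outcome, with a matching test, would also be coherent. It would, however, replace the outcome that the abstract and section 2.6.2 name, which is a larger change than the point requires.

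The cost is a rewording of section 2.8, at most one line in section 2.6.3, and a look at the pre-experimental data. Stating a detectable difference does not in itself alter the planned number of patients.

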### Study setting, recruitment, and informed consent

2.1

The trial will be carried out at the Affiliated Hospital of Chengdu University of TCM. Sixty patients will be recruited by posting recruitment ads on hospital outpatient clinics and hospital ward bulletin boards. A contact number will be included in the recruitment information so that potential participants can contact us. The study will be available to all NBD patients (constipated type) interested in the therapy of “combination 3 methods progression.” Two trained investigators will describe the study to the patients (if applicable), including the purpose, content, duration, and frequency of interventions, benefits, possible discomfort and risks, and associated costs. All patients who agree to participate in this study will sign an informed consent form.

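### The step from 28 to 30 patients per arm is an increase of about 7%, not the stated 20%, and beta is given as 80% where the calculation uses 20%

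*Protocol article*

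**What the plan says.** Section 2.8 (Sample size) gives a formula for comparing two proportions with pooled variance. The inputs are an effective rate of 85% in the intervention group and 50% in the control group (from a pre-experiment), alpha 5%, beta 80%, and quantiles of 1.96 and 0.84. The result is that "the estimated sample size was 28 patients per arm". To make up for lost patients, the section continues, "the sample content is increased by 20%, so the final sample size was 30 patients per arm".

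The figure of 30 per arm carries through the rest of the article. Section 2.1 states that "Sixty patients will be recruited", the abstract gives the same total, and section 2.4 fixes equal allocation: "Patients will be randomized at a 1:1 ratio into intervention group and control group". No section gives another loss rate or another reason for 30.

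**The concern.** Three legible numbers in one short passage (28, 20% and 30) do not fit together, since adding a fifth to 28 cannot give 30. This calculation sets the enrolment target, so a reader of section 2.8 would credit the trial with a larger reserve against loss than it has. If losses came near the size of the stated increase, the number of evaluable patients would fall below the 28 per arm that the plan itself calculated.

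The beta entry adds to the difficulty. Beta is the type II error rate, so 80% read literally means 20% power. The paragraph never names power in words, and the reader has to recover it from the quantile.

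**Working it through.** **Inputs** (section 2.8; the 1:1 ratio is from section 2.4)
- P1 = 0.85, P2 = 0.50, so delta = 0.35 and P = (0.85 + 0.50)/2 = 0.675
- P(1 − P) = 0.675 × 0.325 = 0.219375
- quantiles 1.96 (two-sided 5%) and 0.84 (power 80%, beta 20%)
- stated increase 20%; stated result 30 per arm

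**Step 1: the plan's base figure**

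n = 2 × (1.96 + 0.84)² × 0.219375 / 0.35² = 2 × 7.84 × 0.219375 / 0.1225 = 28.08

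This reproduces the stated 28. Strict rounding up would give 29, a difference of no consequence here.

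**Step 2: the increase**

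| Reading of the 20% | From 28 | From 29 |
|---|---|---|
| n × 1.2 | 33.6, so 34 (68 in total) | 34.8, so 35 |
| n / 0.8 | 35 (70 in total) | 36.25, so 37 |

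Neither reading gives 30.

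**Step 3: what 30 per arm provides**
- Increase over 28: 30/28 − 1 = 7.1%
- Loss tolerated before falling below 28: 1 − 28/30 = 6.7%
- Loss tolerated before falling below 29: 1 − 29/30 = 3.3%

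**Step 4: power for 85% versus 50% with fewer evaluable patients**

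A 20% increase offsets a loss of 1 − 1/1.2 = 16.7%, which leaves 30/1.2 = 25 per arm. A 20% loss leaves 30 × 0.8 = 24 per arm.

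Three methods were used:
- (a) the plan's formula inverted: Φ(0.35 × √(n / 0.43875) − 1.96), where 0.43875 = 2 × 0.219375
- (b) pooled variance under the null and separate variances under the alternative: Φ((0.35√n − 1.96 × √0.43875) / √0.3775), where 0.3775 = 0.85 × 0.15 + 0.50 × 0.50
- (c) exact enumeration of the Pearson chi-squared test, which section 2.9 names for categorical variables

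| Evaluable per arm | (a) | (b) | (c) |
|---|---|---|---|
| 30 (no loss) | 82.5% | 84.3% | 84.7% |
| 28 | 79.8% | 81.6% | 83.1% |
| 25 (16.7% loss) | 75.2% | 76.9% | 79.0% |
| 24 (20% loss) | 73.5% | 75.1% | 76.7% |

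Example for (a) at n = 24: 0.35 × √(24/0.43875) = 2.589; 2.589 − 1.96 = 0.629; Φ(0.629) = 0.735.

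**Step 5: could another formula explain 30?**

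With unpooled variance throughout, the base is 24.2, rounded up to 25, and 25 × 1.2 = 30. But section 2.8 prints the pooled formula and a base of 28, so this does not rescue the sentence.

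**The case against.** The best defence concerns the consequence, since the arithmetic itself cannot be defended. With no loss, 30 per arm exceeds 80% power by every method. With 25 remaining, the exact test gives 79.0%, only 1 point short. The largest shortfall in the table is 6.5 points. The abstract claims only preliminary evidence of efficacy. The beta entry changes no number, because the quantile used is the one for 80% power, and reporting 28.08 as 28 is trivial. All of this stands, and it limits how much weight the point can bear.

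Three stronger readings might be inferred, and the document does not support them.
- *The plan expects 20% of patients to be lost.* Section 2.8 states an increase of 20% to replace losses and gives no expected loss rate. Taken literally, that increase offsets 16.7% loss, so the row for 25 per arm must be shown beside the row for 24.
- *The trial misses a stated power of 80%.* No power is stated. The 80% is inferred from 0.84, and the inference is sound only once beta = 80% is treated as a slip.
- *The trial is underpowered for its primary outcome.* The calculation concerns an effective rate, while section 2.6.2 makes the weekly count of spontaneous bowel movements primary. The power figures here say nothing about that count.

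None of these limits makes 28 plus 20% equal to 30.

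**Conclusion.** Section 2.8 is wrong as written in two places. The stated increase of 20% is in fact 7.1%, so the printed rule would give 34 per arm (or 35 if read as an allowance for 20% loss), which is 4 to 5 more per arm than planned. The stated beta of 80% should be 20%.

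The enrolment figure needs a correct justification, but the trial is not invalidated. Power for the rate comparison is about 82% to 85% with no loss, falling to about 74% to 79% at losses of 16.7% to 20%. These values assume the plan's own rates of 85% and 50%, a two-sided 5% level (implied by 1.96, not stated in words) and equal loss in the two arms. The document does not say how much loss will occur, so it does not establish that the shortfall will arise.

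**What to change.** Keep 60 patients and restate section 2.8, for example:

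*Beta = 20% (power 80%). The formula gives 28.08, taken as 28 per arm. The planned 30 per arm is an increase of about 7% and allows about 6.7% loss (3.3% if 28.08 is rounded up to 29). For the comparison of effective rates (85% vs 50%), power is about 82% to 85% with no loss, about 75% to 79% if 25 per arm remain (16.7% loss, the loss that a 20% increase would offset), and about 74% to 77% if 24 per arm remain (20% loss). These figures apply to the effective-rate comparison used for planning, not to the weekly number of spontaneous bowel movements.*

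The cost is a few lines of text and a slightly less favourable stated power under loss. The total in the abstract and section 2.1 is unchanged, and no extra patients are needed. If the sponsor prefers to keep the 20% increase, the number must change instead, to 34 per arm from a base of 28 (35 if the 20% is meant as a loss rate), and the total of 60 must change wherever it appears.
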